### Research group

2.3

Based on the TC level, we divide patients into 3 groups, and the correlation between the TC and the degree of CAS is evaluated. With or without HTN will be further stratified to assess the effect of with or without HTN on the correlation between TC levels and the degree of CAS. The 6 subgroups are: NTC/-HTN group, NTC/+HTN group, BHTC/-HTN group, BHTC/+HTN group, HTC/-HTN group, HTC/+HTN group. The NTC/-HTN group is taken as the reference group. The flow diagram is shown in Figure 1.

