## Introduction

1

Coronary heart disease (CHD) is a heart disease that is caused by myocardial ischemia, hypoxia, or necrosis because of coronary stenosis, or occlusion of coronary atherosclerosis.^[1]^ Angina pectoris is typical in clinical and closely associated with inadequate coronary blood supply; it can seriously affect the life and work of patients and families. Therefore, the prevention and treatment of angina pectoris should be taken into consideration.^[2–4]^ According to a report released in 2017 by the International Cooperation Study on the Global Burden of Disease, CHD is the leading cause of death in all diseases globally, with an estimated 110 million people suffered from CHD and 8.92 million deaths due to CHD, and the prevalence continues to rise.^[1,5]^ Evidence-based medicine and a large number of clinical epidemiological investigations show that hypercholesterolemia and hypertension (HTN) are risk factors for CHD angina pectoris.^[6]^ Hypercholesterolemia has resulted in 4 million deaths and a disability-adjusted life loss of up to 88.7 million people globally.^[7]^ Through multiple studies of risk analysis of CHD angina pectoris, HTN is generally regarded as an important risk factor for CHD angina pectoris.^[8]^ Combined with Gensini scoring system, Coronary angiography (CAG) makes a precise diagnosis of the number, location, scope, and vascular wall of coronary artery stenosis (CAS),^[9]^ CAG is regarded as the best way to diagnose CHD and the most powerful method of evaluating the degree of CAS.^[10]^

According to the report, some scholars have conducted combined studies of hypercholesterolemia and HTN. Still, no studies have reported the influence of HTN on the correlation between hypercholesterolemia and the degree of CAS. Therefore, we conduct a retrospective study to explore the relationship between hypercholesterolemia and CAS and whether its relationship is affected by HTN. Through clinical data, we will provide guidance for the prevention and treatment of CHD angina pectoris complicated with diseases and promote further research.

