### Statistical analysis

2.6

Before performing statistical analysis, we shall invite statistical analysts to make plans and specify detailed steps, then carefully examine the data collected. All statistical analysis processes are programmed and archived for future reference.

#### 
Statistical methods

2.6.1

1.Continuous variables conforming to the normal distribution are expressed by standard deviation and mean, and the difference between groups is analyzed by one-way ANOVA.2.If it conforms to non-normal distribution, we use the median, upper quartile (Q1), lower quartile (Q3), 95% confidence interval to express, and rank-sum test (Wilcoxon method) for analysis.3.The classified data are expressed in terms of quantity and percentage and analyzed by the χ^2^ test and Fisher exact probability method.4.If considering the influence of baseline confounding factors, logistic regression analysis is used. The correlation between variables is analyzed by Spearman or Pearson correlation.

We use SPSS version 23.0 (IBM Corporation, Armonk, NY) to conduct all analyses. The general statistical test uses a bilateral test, and bilateral *P* < .05 is considered statistically significant.

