## Discussion

3

In China, the death rate of cardiovascular disease still ranks first, accounting for more than 40% of the death rate of residents, and it is much higher than the death rate of tumors and other diseases.^[17]^ According to a report released by the Chinese Expert Consensus on the Comprehensive Management of BP and lipids in hypertensive patients (2019), there are currently about 245 million HTN patients in China. Among the patients with HTN screened by the population, those with at least 1 dyslipidemia accounted for 41.3%, and those with hypercholesterolemia were 9.9%.^[18,19]^

Studies have found that hypercholesterolemia and HTN have both separate and synergistic effects on the occurrence of CHD. The combination of the 2 effects is not a simple superposition effect, but an amplification effect or a product effect. The synergy may be realized through several direct and indirect mechanisms. Endothelial injury theory or oxidized LDL endothelial injury theory may be the initiating mechanism of cholesterol deposition on the arterial wall. Recent studies have found that endothelial cells can maintain hemodynamic stability and affect the process of CHD by producing nitric oxide (NO) and angiotensin-II (AT-II).^[20]^

This study has the following advantages:

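### The protocol asks whether hypertension modifies the cholesterol–stenosis relation, but none of its named analyses tests a TC × HTN interaction or compares the TC effect between HTN strata

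*Protocol article*

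**What the plan says.** The Introduction sets out to "explore the relationship between hypercholesterolemia and CAS and whether its relationship is affected by HTN". The Research group section (2.3) repeats this. It first evaluates TC against the degree of stenosis in three TC groups, then stratifies by hypertension "to assess the effect of with or without HTN on the correlation between TC levels and the degree of CAS". It forms six TC × HTN cells and adds: "The NTC/-HTN group is taken as the reference group".

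Statistical methods (2.6.1) lists the tools. For normally distributed variables, "the difference between groups is analyzed by one-way ANOVA". For other continuous variables it names a "rank-sum test (Wilcoxon method) for analysis". Categorical data get χ² and Fisher tests. On adjustment: "If considering the influence of baseline confounding factors, logistic regression analysis is used". Associations between variables are examined by Spearman or Pearson correlation. Tests are two-sided at 0.05.

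The protocol article names no product term, two-way model, homogeneity test across HTN strata or comparison of correlations between strata. The total is 1000 cases, with no expected cell sizes, effect sizes or power.

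**The concern.** Whether hypertension changes the TC–stenosis relation is a question about a difference of differences (or of slopes). Each listed method answers another question: whether any of several groups differ, whether one cell differs from another, whether two variables are associated, or whether an association survives adjustment.

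A study that follows the list would report which cells differ from NTC/-HTN and perhaps one correlation per HTN stratum. It would give no estimate, interval or p-value for modification. If HTC/+HTN were significant and HTC/-HTN were not, a reader could easily conclude that hypertension strengthens the TC effect. That pattern is common when the two factors simply add. A real modification, in turn, would go unquantified.

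**Working it through.** **Step 1. Match each named method to the question.**
- One-way ANOVA over six cells tests equality of all six means. It rejects for a TC effect, an HTN effect or an interaction, and does not say which.
- The rank-sum test makes the same kind of group comparison on ranks.
- Cell versus NTC/-HTN: for HTC/+HTN this measures the TC effect, the HTN effect and any interaction together.
- Logistic regression is named for baseline confounding only.
- Correlations split by HTN describe the relation in each stratum. Nothing compares them.

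The quantity the question needs is (HTC − NTC within +HTN) − (HTC − NTC within −HTN), or the difference between the two TC slopes. It is not named.

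**Step 2. What the named comparisons show when there is no interaction.** The protocol gives only N = 1000 and two-sided 0.05. All else here is assumed: TC shares 75/17/8%, HTN prevalence 65%, 75% or 85%, score SD of 1, HTC +0.4 SD, HTN +0.2 SD, strictly additive.

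The standard error of a cell-versus-reference difference is sqrt(1/n_cell + 1/n_ref). At 75% HTN:
- NTC/-HTN has 187.5 patients, HTC/-HTN 20 and HTC/+HTN 60.
- HTC/-HTN: true difference 0.4, SE = sqrt(1/20 + 1/187.5) = 0.235, power 40%.
- HTC/+HTN: true difference 0.4 + 0.2 = 0.6, SE = sqrt(1/60 + 1/187.5) = 0.148, power 98%.

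Simulating the cell means, with the shared reference, gives:

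| HTN prevalence | HTC/+HTN significant, HTC/-HTN not | Reverse pattern | Interaction contrast rejects |
|---|---|---|---|
| 65% | 47% | 0.9% | 5% |
| 75% | 59% | 0.5% | 5% |
| 85% | 72% | 0.4% | 5% |

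The discordance nearly always points towards amplification, although none exists. The interaction contrast on the same data keeps its nominal 5%.

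**Step 3. A second set of assumptions.** Take HTC and HTN effects of 0.3 SD each, additive, HTN share 50% to 80%, and TC shares from equal thirds to 70/20/10%.
- With identical true TC effects in both strata, HTC versus NTC is significant in one stratum and not in the other in 34% to 63% of studies.
- At 70% HTN and 60/25/15% TC shares (with BHTC at +0.15 SD), six-group ANOVA rejects in 99.6% of simulations and the 2-df interaction test in 5.6%.
- With an HTN effect and no TC effect at all, ANOVA still rejects in 94% and the interaction test in 5.1%.

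**Step 4. Precision of the missing test.** For the HTC-versus-NTC interaction contrast, SE = sqrt(sum of 1/n over the four cells), and the effect detectable at 80% power is (1.96 + 0.84) × SE = 2.80 × SE. With the Step 2 shares:
- 65% HTN (262.5, 487.5, 28, 52): SE 0.247, detectable 0.69 SD.
- 75% HTN (187.5, 562.5, 20, 60): SE 0.272, detectable 0.76 SD.
- 85% HTN (112.5, 637.5, 12, 68): SE 0.329, detectable 0.92 SD.

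With continuous TC at 75% HTN, SE = sqrt(1/750 + 1/250) = 0.073, so 0.20 SD per SD of TC is detectable. For normally distributed TC, the mean gap between the lowest 75% and the highest 8% is about 2.28 SD, so this is about 0.47 SD over that gap. The gain holds only if the relation is close to linear.

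**The case against.** Much of the opposing case is fair.

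- **A reader might infer that the design cannot answer the question.** It can. Six cells are a saturated layout, and the interaction is a contrast of the same cell means. The reference cell is not an error. Only a named contrast is absent.
- **Stratified correlations are a natural reading of 2.3.** They bear on the question descriptively. They still lack a comparison, and a correlation coefficient also depends on the spread of TC within its stratum.
- **Modification is not the only aim.** The study title concerns hypercholesterolemia alone or combined with hypertension, and a common-reference comparison suits that joint-effect question.
- **The Discussion might be read as this study's hypothesis**, because it says "The combination of the 2 effects is not a simple superposition effect, but an amplification effect or a product effect". That sentence reports earlier findings on the occurrence of CHD. It does not set this study's hypothesis and is not relied on here.
- **A reader might infer that the authors intend to claim amplification from significance patterns, or that unequal cells inflate differences.** The document states no such inference rule. Unequal cell sizes change precision and significance, not the expected difference.
- **Detail is deferred.** Section 2.6 leaves detailed steps to statistical analysts, and a later plan could add the test. However, the protocol itself fixes a reference cell and a method list that do not match its own question. A later plan faithful to that list would still not test modification.

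**Conclusion.** The point holds in a limited form. The Introduction and 2.3 ask whether hypertension modifies the TC–stenosis relation, and the analyses named in 2.3 and 2.6.1 give no test or interval for it. They cannot, as named, tell additive effects from modification. The data to be collected can.

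The 47% to 72% is illustrative. It rests on assumed prevalences, TC shares and additive effects, and does harm only if differing significance is read as modification. The structural mismatch does not depend on these figures. Whether 1000 cases suffice for the interaction cannot be judged from the document.

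Interaction also depends on scale. Effects that add on the raw score need not add on the log scale, and effects that multiply may show little interaction after a log transformation. The test therefore means little until the scale is fixed.

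**What to change.** In 2.6.1, add for the HTN question one regression of the Gensini score (GS) on TC, HTN and TC × HTN, adjusted for the confounders already collected under 2.4. Before database lock, fix:

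- **The scale.** For example log(GS + 1), stating that interaction is then judged multiplicatively, or untransformed GS with robust standard errors for additive interaction.
- **The form of TC.** Either the protocol's three groups (2-df test) or continuous TC. Continuous TC is likely to be more precise if the relation is near linear.

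Report the TC effect in each HTN stratum, and the interaction estimate with its 95% confidence interval and p-value. Keep the six-cell comparison with NTC/-HTN to describe the joint effect, and state that it is not a test of modification.

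The cost is about one paragraph, with no new data or patients. The downside is that the interaction may be estimated imprecisely at N = 1000. The report should say so, and a non-significant result should not be read as absence of modification.

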**Figure 1 F1:**
[figure not shown]
The flow diagram of effect of hypercholesterolemia alone or combined with hypertension on the degree of coronary artery stenosis in patients with coronary heart disease angina pectoris: a medical records based retrospective study.

### Observation indicators

2.4

In the hospital medical record management system, we collect the clinical data of the first day of hospitalization of the patients, which include demographics such as age, gender, ethnicity, weight, smoking, medical history, BP; clinical biochemical tests such as fasting plasma glucose, glycated hemoglobin, TC, Triglyceride, high density lipoprotein cholesterol, low density lipoprotein cholesterol, C-reactive protein, Fibrinogen and other indicators; CAG data in imaging examination.

According to the location and degree of the lumen stenosis, the score of the degree of each CAS is calculated. In order to calculate Gensini score (GS), the percentage diameter of the stenosis is assigned based on the severity of the stenosis (from 0–32): 1 point for stenosis ≤ 25%, 2 points for stenosis 26% to 50%, 4 points for stenosis 51% to 75%, 8 points for stenosis 76% to 90%, 16 points for stenosis 91% to 99%, and 32 points for stenosis 100%. Lesion site score: 5 points for left main coronary artery, 2.5 points for proximal left anterior descending (LAD), 1.5 points for middle LAD, 1.0 point for distal LAD, 1.0 point for the first diagonal branch, 0.5 points for the second diagonal branch, 2.5 points for proximal left circumflex (LCX), 1.0 point for distal LCX, 1.0 point for blunt LCX, 1.0 point for posterior descending branch, 0.5 points for posterior branch and 1.0 point for right coronary artery. Multiply the stenosis score by the lesion site score, then add all the scores we will get the final GS, which is defined by 2 independent doctors.^[15,16]^ The data of CAG were separately defined by more than 2 interventional doctors who did not know the rest data of patients, and a third doctor will participate in the analysis if necessary. The GS rule is shown in Table 1.

**Table 1 T1:**
[figure not shown]
The Gensini score rule.

### Data management

2.5

#### 
Quality assurance

2.5.1

To carry out the research smoothly, the research team will hold a special clinical training meeting before the formal launch of the clinical trial and provide researchers with centralized training in each center.

Conduct training on the project implementation program and standard operation procedure (SOP) to make every researcher has an intimate knowledge of the process of study and specific operation method, so as to promote the consistency of internal observations among researchers and between observers, and ensure the reliability of clinical research conclusions.

Sign the investigator's statement and establish SOP for observation and quality control of various indicators in the laboratories of participating hospitals.

Quality control measures of each center. Conduct regular audits of the centers to control the bias between the centers.

#### 
Original data management

2.5.2

We use the paper case report form (CRF); those will be valid after being checked and approved by the researchers. All CRFs, as well as the modification process, will be preserved.

#### 
Data entry

2.5.3

Double data entry is performed using Epidata 3.1 (Jens M. Lauritsen, Odense, Denmark) database, and 2 qualified professionals will enter the data into the computer separately. Before data entry, we will conduct specialized entry training for relevant individuals. They will enter data based on the entry guide formulated according to the research content.

#### 
Medical coding

2.5.4

Medical coding is performed by specialized data managers with a medical background. The coding content is medical history. The medical history will be coded according to MedDRA dictionary (Version 13.0). The encoded documents will be sent to the main researchers for review and confirmation in the form of electronic documents.

#### 
Writing of data verification and answers to questions

2.5.5

We will carefully check the entered data one by one based on the data verification plan (SAP). SAP should be signed and approved by the data managers and statisticians.

We use 2 verification methods, including systematic verification and manual medical verification. The former mainly uses SAS 9.3 (SAS Institute Inc., Cary, NC) software to write programs and then generates a data clarification form (DCF). All data queries discovered by the 2 methods will be entered into the data query database, a formal DCF will be produced by the data management. DCF will be handed over to research inspectors after being checked. After re-inspection, inspectors will submit DCF to researchers in each center for further inspection and reply. Only after receiving the DCF with the researcher's signature and date, can we modify the database. It will be placed in the project-special file cabinet for storage. All modifications to the database will be recorded.

#### 
Database locking

2.5.6

The database will be locked when it meets the following requirements:

All questions (including those raised at the data review meeting) have been resolved, and the database has been updated.No new questions were found in the data verification.The medical coding has been completed and approved by the applicant.The crowd division plan has been approved.SAP has been finalized and approved by the project leader.

The head of DSMB, statistician and data administrator jointly sign the database locking form, while the database is locked. After the database is locked, any change of data must be approved by the project leader and filed by the data management unit.

The overall process of data management is shown in Figure 2.

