**Methods::**

A multicenter, retrospective clinical study was conducted in the medical records management system of 6 hospitals in Tianjin. Patients who were suffered from CHD angina pectoris and aged from 35 to 75 years old are involved. They hospitalized in the Department of Cardiology between September 1, 2014, and September 1, 2019, and underwent coronary angiography. We divide patients into 3 groups based on the total cholesterol level, the degree of CAS is evaluated by Gensini score, and further divide them into 6 subgroups based on with or without HTN. Collect and analyze the demographics, laboratory information, clinical outcome data, and coronary angiographic data of patients.

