### Study design

2.1

We carried out a multicenter, retrospective clinical study. The collaborative network of CHD research medical units formed by the research team includes the first affiliated hospital of Tianjin University of traditional Chinese medicine (TCM), the second affiliated hospital of Tianjin University of TCM, Tianjin Nankai Hospital, the affiliated hospital of Tianjin Institute of TCM, Tianjin Chest Hospital and Tianjin Medical University General Hospital. The cases of 1000 patients meeting the diagnostic, inclusion and exclusion criteria were collected through the hospital medical record management system.

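### Audits and laboratory SOPs cannot remove hospital differences already fixed in the 2014–2019 records, and the pooled tests carry no hospital term, so hospital can confound the TC–GS and TC-by-HTN comparisons

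*Protocol article*

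**What the plan says.** The design is a retrospective record review: "A multicenter, retrospective clinical study was conducted in the medical records management system of 6 hospitals in Tianjin". Section 2.1 names the hospitals, which include TCM hospitals, a chest hospital and a university general hospital, and sets the size: "The cases of 1000 patients meeting the diagnostic, inclusion and exclusion criteria were collected through the hospital medical record management system". Section 2.2.2 limits admissions to 1 September 2014 to 1 September 2019.

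TC and blood pressure come from the record; under section 2.4, "we collect the clinical data of the first day of hospitalization of the patients". The angiographic outcome is read by blinded doctors: "The data of CAG were separately defined by more than 2 interventional doctors who did not know the rest data of patients". A third doctor joins if needed.

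Section 2.5.1 deals with consistency across centres in three ways:
- training: "the research team will hold a special clinical training meeting before the formal launch of the clinical trial";
- laboratory procedures: "establish SOP for observation and quality control of various indicators in the laboratories of participating hospitals";
- audits, the only measure tied explicitly to between-centre bias: "Conduct regular audits of the centers to control the bias between the centers".

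For normally distributed variables section 2.6.1 states that "the difference between groups is analyzed by one-way ANOVA". It adds a rank-sum test for non-normal data, chi-square or Fisher tests for categories, and Pearson or Spearman correlation. Logistic regression is offered if baseline confounders are to be considered. Hospital is named in none of these.

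**The concern.** Patients are not randomised to TC groups, so nothing in the design balances hospitals across normal, borderline-high and high TC. If hospitals differ both in TC distribution and in typical angiographic severity, pooling turns those differences into an apparent TC–GS association, or hides a real one. The same applies to the six TC-by-HTN subgroups, since HTN status also depends on recorded diagnosis, treatment and blood pressure.

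There are two plausible sources, neither of which the stated measures can reach. One is case mix: a chest hospital and a TCM hospital may admit different angina patients. The other is assay calibration: TC groups are cut at fixed values (5.18 and 6.19 mmol/L), so a difference between laboratories moves patients across a boundary. Audits and SOPs introduced for this study act on what is done from now on, whereas both sources lie in records that already exist.

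**Working it through.** **What each measure can reach**

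| Item | When fixed | Can training, SOPs or audits change it? |
|---|---|---|
| TC, blood pressure | First day of admission, 2014–2019 | No, only whether they are transcribed correctly |
| Hospital case mix | Admission, 2014–2019 | No |
| Record abstraction, HTN coding | During the study | Yes |
| GS from the angiograms | When scored by the readers | Yes, if scored during the study |

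That the SOPs postdate the data is an inference from the future tense in 2.5.1 and the 2020 in the ethics approval number (2.7). No SOP date is printed.

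The article has no figure to reproduce: the 1000 patients come without an SD, effect size or power, and no between-hospital variation is given. Every hospital contrast below is therefore an assumption.

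**Check 1: size of the spurious difference.** Assume two equal hospital blocks, no TC effect within a block, and a GS gap d between blocks. If shares a and b of the blocks have TC ≥ 5.18, the first block makes up a/(a+b) of the raised-TC patients and (1−a)/(2−a−b) of the normal-TC patients. The false difference in mean GS is

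d × [a/(a+b) − (1−a)/(2−a−b)].

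- 35% vs 15%: 0.35/0.50 − 0.65/1.50 = 0.700 − 0.433 = 0.267, so 2.7 points at d = 10 and 5.3 at d = 20.
- 30% vs 20%: 0.600 − 0.467 = 0.133, so 1.3 and 2.7 points.
- 27% vs 23%: 0.540 − 0.487 = 0.053, so 0.5 and 1.1 points.

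**Check 2: type I error of the pooled three-group ANOVA.** Same two-block set-up, simulated with 1000 patients and GS SD 30 (assumed):

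| TC ≥ 5.18 in the two blocks | d = 10 | d = 15 | d = 20 |
|---|---|---|---|
| 27% vs 23% | 5.3% | 6.3% | 6.9% |
| 30% vs 20% | 7.3% | 12% | 16% |
| 35% vs 15% | 18% | 33% | 54% |

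At a 5-point gap even 35% vs 15% gives only 7–8%. With a hospital term, rates were 4.3–5.5%.

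**Check 3: six hospitals, random differences.** 1000 patients in six near-equal hospitals, no within-hospital association, and an assumed between-hospital share of variance (ICC) in both TC and GS; 2000 runs each, two-sided 0.05. The ANOVA uses an assumed 60/25/15 split. In the last column hospital means of TC and GS line up perfectly, so the pooled correlation r equals the ICC and rejection is Φ(z−1.96) + Φ(−z−1.96), with z = artanh(r)·√997.

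| ICC | Spearman, pooled | ANOVA, pooled | Hospital removed | Perfectly aligned, pooled |
|---|---|---|---|---|
| 0 | 5.0% | 5.4% | 4.9% | 5.0% |
| 0.01 | 4.7% | 4.8% | 4.6% | 6.1% |
| 0.02 | 6.0% | 5.7% | 5.2% | 9.7% |
| 0.05 | 8.5% | 6.7% | 5.6% | 35% |
| 0.10 | 19.9% | 12.7% | 5.1% | 89% |

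For example, at ICC 0.05, z = 0.0500 × 31.58 = 1.58 and Φ(1.58 − 1.96) = Φ(−0.38) = 0.35.

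**Check 4: laboratory calibration.** With TC mean 4.5 and SD 1.0 (assumed), P(TC ≥ 5.18) = 1 − Φ(0.68) = 24.8%. A laboratory reading 3% high gives 5.18/1.03 = 5.03, so 1 − Φ(0.53) = 29.8%. One reading 5% high gives 5.18/1.05 = 4.93, so 1 − Φ(0.43) = 33.2%.

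**The case against.** The strongest reply is that an article's short list of methods need not name every covariate. Section 2.6 says analysts will specify detailed steps, and nothing excludes hospital, which could enter the logistic regression. This stands in part: the absence of a covariate list alone would be no finding. What remains is that the text does not leave between-centre bias open. It assigns that bias to audits, which cannot deal with the part already in the records. The logistic regression is optional and would need GS to be dichotomised; no cut-off is given.

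Three stronger readings are tempting and are not supported.
- *That the quality measures are useless.* They can act on abstraction, HTN coding and scoring, and section 2.4 adds blinded multiple reading with a third doctor. Common diagnostic criteria, double data entry and centre-level queries also help. None of these corrects assay differences or case mix.
- *That the plan rules out adjustment for confounding.* It does not; the route is conditional and unspecified.
- *That the pooled result will be badly biased.* The documents do not show that the hospitals differ in TC or GS. The rates of 18% to 54% need large, aligned contrasts in two equal blocks, while the article has six hospitals and gives no such figures. Milder contrasts leave the error at about 5–8%.

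**Conclusion.** The point holds as a mismatch between a named problem and its stated remedy. The quality measures in 2.5.1 cannot remove hospital differences already present in recorded TC, blood pressure and case mix, and the pooled comparisons and correlations in 2.6.1 do not remove them either. Hospital can therefore confound the TC–GS and TC-by-HTN results.

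How much is not known. If hospitals differ little (ICC up to about 0.02 with unaligned effects), the type I error is about 5–6% and the matter is negligible. If they differ strongly and TC and GS move together across hospitals, it rises well above 10%. The range rests on assumed GS SD, TC distribution, hospital gaps and ICCs, and is illustrative. Less dependent on those assumptions is the comparison: with hospital in the model the rate stayed near 5% in every scenario simulated.

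**What to change.** 1. In section 2.6.1, state that the main TC–GS and TC-by-HTN analyses include hospital as a six-level fixed effect, for example a linear model for GS with TC group, HTN, their interaction and hospital. Alternatively, use hospital as a stratum, with stratified rank or categorical tests where those apply. A partial correlation given hospital would replace the plain one.
2. In section 2.5.1, limit the audit sentence to the quality of abstraction and scoring, and say that remaining hospital differences are handled in the analysis.

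Transforming or ranking GS and showing estimates by hospital are optional.

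One limit should be acknowledged: a hospital term removes differences in hospital means. It does not move patients back across the 5.18 and 6.19 mmol/L cut-offs if a laboratory reads high or low.

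The cost is wording plus five degrees of freedom out of 1000 patients. No new data should be needed, since the source hospital should be known for every record.
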